**Fig. 3 Fig3:**
[figure not shown]
Flow diagram of selection and randomisation process for the Healthy Start study.

### Main outcome measures

To assess the objectives specified earlier, each of the measures below is administered to participants in the intervention group before and after the intervention period. The measures are administered at the same times to participants in the control group.

### Physical activity level

Children’s physical activity levels are obtained using an Actical accelerometer worn during attendance of ECC for five consecutive weekdays. Accelerometers represent an objective and valid method of measuring physical activity in preschoolers [48–50]. The Actical, an omnidirectional accelerometer, was demonstrated to have higher intra- and inter-instrument reliability than other accelerometers [51]. It correlates at *r* = 0.89 with directly measured oxygen consumption [50]. For this study, accelerometer data are recorded in 15 s intervals. Data will be cleaned and managed using the procedure recommended by Statistic Canada [52, 53] through a series of publicly available SAS codes adapted for this type of study [54].

Educators’ physical activity levels are measured with pedometers (New Lifestyles SW-200 DIGI-WALKER). The SW-200 pedometers, commonly used in applied research, have consistently shown to be among the most accurate at counting steps in controlled laboratory settings [55, 56], and have demonstrated acceptable reliability in real-life settings [57]. Educators are given a log in which to record the number of steps taken each day during work at the ECC for the same five consecutive weekdays.

### Physical literacy

Physical literacy and gross motor skills of children are measured using the Test of Gross Motor Development (TGMD-II). The TGMD-II is a standardized test designed to assess the gross motor functioning of children aged 3 through 10 years [58]. It evaluates two subtests of skills: locomotor (run, hop, gallop, leap, horizontal jump and slide) and object control (ball skills such as striking a stationary ball, stationary dribble, catch, kick, overhand throw, and underhand roll). Of the 12 skills included in the TGMD-II, three (slide, striking with a stationary ball and stationary dribble) are not assessed as they were found particularly difficult and rarely performed adequately by children under six years in pilot work. This was decided in concertation with developers of the TGMD-II. Each child is videotaped while completing the skills. Videos are then reviewed by trained researchers who score two trials for each subtest. Moderate to strong correlations were reported between the TGMD-II and the Comprehensive Scales of Student Abilities, and an inter-rater correlation coefficient of 0.98 indicate good test-retest reliability [58].

### Quality of food served to children

Menus and recipes for mixed dishes are collected from each ECC. From these, the types and amounts of meals and snacks served are recorded. Information on food provided is standardized in terms of category and food group as well as number and portion size served.

### Food consumed by children

Food intake in ECCs is assessed using the digital photography-weighted plate waste method on two consecutive days. Food consumed is measured by weighing each food served to participants with a digital scale that was manually calibrated (inStyle, 16 × 22 × 1.5 cm, Home Hardware Stores Limited, Canada, 2009) and simultaneously taking a digital picture of the food, and the plate ware on which it was served, with an “ASUS Memo Pad HD7” (ME173X model, Android US, China, 2013). Any leftovers of those foods are then weighed and pictured again at the end of the meal. This is done for every serving. Pictures are taken at a distance of 62 cm and at a 45° angle [59]. This method has been extensively used in studies of school-aged children [60–62] and is considered the most precise measurement of dietary intake [63, 64]. Digital photography has recently been used to characterize meals served and consumed at pre-schools and it is correlated at 0.92 (*p* < 0.0001) with the weighing method [59]. Information on amount of calories, various food groups, macronutrients, vitamins and minerals consumed is derived by subtracting the weight of leftover of a given food from the weight served. For foods containing multiple food groups, trained research assistants used the pictures to estimate the proportion of food group consumed. This step is assisted by the Food Processor nutritional analysis software (Food Processor, Esha version 10.10.00).

### Eating habits and nutritional risks

The Nutrition Screening Tool for Every Preschooler (NutriSTEP), designed and validated in both English and French for 3–5 year-old Canadian children of different ethnicities, is used to assess eating habits and nutrition problems in children [65]. This screening tool consists of 17 questions and takes parents or primary caregivers about five minutes to complete. Assessment of nutritional risk using the NutriSTEP has been validated against registered dietitians’ nutrition assessments (*r* = 0.49, *p* = 0.01) [66]. Intraclass correlation of 0.89 (*p* < 0.001) indicates good test-retest reliability and the majority of items have a Kappa percent of agreement ranging from adequate (κ > 0.5) to excellent (κ > 0.75) [66]. NutriSTEP includes a validated semi-quantitative food frequency questionnaire to assess the usual intake of fast foods as well as the four main food groups according Canada’s Food Guide to Healthy Eating: fruits and vegetables, milk and alternatives, meat and alternatives, grain products. This enables us to estimate the contribution of meals consumed in ECCs to the total intake of the four main food groups.

### Early childcare centre environment

Dietary and physical activity practices and policies in ECC are measured using items from the Nutrition and Physical Activity Self-Assessment of Child Care (NAP SACC) [67–69]. The 55-items of the NAP SACC retained for this study collect information on 5 components of nutrition (25 items assessing: feeding environment, feeding practices, menus and variety, education and professional development, policy) and 5 components of physical activity (30 items assessing: time provided, indoor and outdoor play environment, educator practices, education and professional development, policy) [70]. Each item is attributed a score between 0 and 3 points. The NAP SACC is filled out independently by two research assistants in each ECC over the course of 2 consecutive days. Differences in item scores are discussed between research assistants, who then come to a consensus. NAP SACC showed excellent inter-rater reliability with 65 % of items having 100 % agreement and all other items having agreement scores exceeding 71 %.

*Knowledge, attitudes, practices and self-efficacy of educators and directors* is measured through a self-administered questionnaire. The educator questionnaire collects information on educator practices related to nutrition (12 items, e.g., role modelling healthy food choices) and physical activity (6 items, e.g., incorporating physical activity into classroom routines and transitions) [68], on their self-perceived knowledge of fundamental movement skills (4 items, e.g., level of knowledge of activities that incorporate motor skills in the daily activities of preschoolers), on their self-efficacy (e.g., rate your level of confidence in …) to promote physical activity (1 item), and to teach fundamental movement skills (1 item) [71, 72]. Educators also provide information on their physical activity level through the International Physical Activity Questionnaire-Short form [73], food choices based on an adapted version of the NutriStep, and sociodemographic information (including their age group, level of education, and the length of time that they have been working as an educator).

### Complementary measures or co-variables

Beyond the main measures which relate directly to the objectives, the following measures are also administered at the beginning and the end of the study to account for potentially confounding factors in the analyses and to assess secondary outcomes.

### Sociodemographic information

Parents provide sociodemographic information through a self-reported questionnaire. Questions in the questionnaire are drawn from Statistic Canada’s Canadian Community Health Survey [74]. The questionnaire provides information on parents’ education levels (highest level of education completed by each parent), family structure (number of siblings and family status) and socioeconomic level (estimate of total family revenues, before deductions, in the last 12 months). Parents also report their physical activity levels and food choices based on the same questions as the educator questionnaire. Parents’ perception of their child’s physical activity abilities are assessed through 4 items of the Perceptions of Physical Activity Importance and their Children’s Ability Questionnaire (PPPAICAQ) [75]. The NutriStep questionnaire is also completed by parents.

### Body composition

Height, weight and waist circumference of children are measured using a standardized protocol [76]. Two measures of height (SECA Stadiometer – Model 213) to the nearest 0.1 cm, weight (SECA Scale – Model 761) to the nearest 0.2 kg, and waist circumference to the nearest 0.1 cm are obtained for each participant. If discrepancies greater than 0.5 cm for height and waist circumference or 0.2 kg for weight are observed between the two measures, a third measure is obtained. The average of the two closest measures is recorded. Body mass index (BMI), calculated using the ratio of weight (kg) and squared height (m^2^) will be used to determine if children are overweight or obese by following the International Obesity Task Force age-adjusted thresholds as recommended [77].

### Training of research assistants

Before every data collection periods, research assistants are given a full day of training on data collection and entry to ensure that all procedures are standardized across sites. Research assistants are trained specifically on how to collect anthropometric data, how to conduct plate waste analysis, and how to complete the environmental scan. They also practice all fundamental movement patterns so that they can demonstrate them correctly, and review how to properly videotape children’s movements. Databases are also presented, and research assistants are trained on how to enter all data collected. Provincial study coordinators oversee all aspects of data collection and data entry to ensure protocols are applied as intended.

### Data analysis

As a first step, each variable distribution will be examined in order to manage obvious errors such as outliers or questionable input. If necessary, appropriate transformations will be applied. If there are systematic missing variables, these will be filled using multiple imputation methods. After the initial data cleaning and processing, descriptive analyses will be used to characterise the two groups of participants and their context.

Analyses of the main study objectives will adhere to the intention-to-treat principle. Multiple linear regression will be used to determine if, in comparison to participants in the usual care group, participants exposed to Healthy Start-Départ Santé had greater increases in ECC-provided opportunities for physical activity, ECC-provided opportunities for healthy eating, in physical activity levels, in healthy eating behaviours, and if they had greater improvements in physical literacy. A multilevel approach will be used in each model to account for clustering that could result from children attending the same ECC. Potentially confounding variables (i.e., age, parental education, household income, etc.) will be included in the models.

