### Target population and sampling

Participants for the Healthy Start-Départ Santé project are recruited from 61 French and English ECCs in two Canadian provinces: New Brunswick and Saskatchewan. Province-specific recruitment and data collection are carried through a study coordinating center established in each province. Both coordinating centers follow the same protocols. Specifically, a registry of all licenced ECCs in both provinces is obtained. From this list we exclude any ECC which has already received a physical activity or nutrition promoting intervention in the past. This avoids underestimating the effect of the Healthy Start-Départ Santé intervention. To be included in the study, an ECC has to prepare and provide meals for lunch. This is required for assessing the quality of foods being served and for measuring nutritional intake. For feasibility and efficiency reasons, the number of children attending the ECC also serves as an exclusion criterion; centers with less than 20 children between the ages of 3 and 5 are not considered. Information on these criteria is obtained from governmental partners or through a brief telephone administered questionnaire. In order to obtain a final sample of at least 735 children, we estimated that a minimum of 15 children aged 3 to 5 would need to be recruited in 62 ECCs. A minimum of 20 children per center was established to account for a 60 % participation rate (Recruiting 60 % of eligible children in 62 ECCs would give a total of approximately 744 participants). Despite planned measures to minimize losses to follow-up, this issue is inevitable in a longitudinal study of this nature. Based on pilot work, we anticipate an attrition rate of approximately 5 %, which will provide adequate statistical power to conduct the planned analyses. The target of 735 children was based on estimates that 700 (735 - 5 %) participants divided into two groups of 350 participants will provide 80 % power to detect a 10 % between-group difference in outcome considering a within-group standard deviation of 40 %, α = 0.05, intra-class correlation of 0.02, and collinearity between the intervention and other explanatory variables expressed by an estimated multiple correlation of 0.15.

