### Limitations

Educator turnover is common in ECC, meaning that new educators in centers offering the Healthy Start-Départ Santé intervention may not receive the intended training. Two elements of the intervention nevertheless reduce this possibility. First, one booster session per centre is offered as part of the intervention to reinforce the training of educators who are there since the beginning and to ensure that others are trained to implement Healthy Start-Départ Santé. Second, Healthy Start-Départ Santé is designed to be integrated into centres’ everyday functioning so that all employees should be exposed to it naturally. Also, children’s physical activity level and dietary intake can vary from one day to the next. This could cause the data to be non-representative of typical behavior. Data collection over five consecutive days for physical activity and two consecutive days for dietary behavior will help minimise this risk.

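### The analysis is worded as a comparison of increases and does not name the baseline value of the outcome as a covariate, though it is measured in both arms

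*Protocol article*

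**What the plan says.** The Data analysis section states that multiple linear regression, with a multilevel approach for clustering by centre, will determine whether, relative to usual care, "participants exposed to Healthy Start-Départ Santé had greater increases in ECC-provided opportunities for physical activity", and likewise for healthy-eating opportunities, then "in physical activity levels, in healthy eating behaviours, and if they had greater improvements in physical literacy". It does not say whether the dependent variable is the follow-up value or the change from baseline.

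On adjustment it says: "Potentially confounding variables (i.e., age, parental education, household income, etc.) will be included in the models". The list is open-ended. The baseline value of the outcome is neither named nor excluded.

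Baseline values will be available. Under Main outcome measures, "each of the measures below is administered to participants in the intervention group before and after the intervention period", and for the other arm, "The measures are administered at the same times to participants in the control group".

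**The concern.** Read plainly, the quantity compared between arms is change from baseline, adjusted for sociodemographic variables. An analyst could follow that text to the letter and regress an unadjusted change score. This fixes the coefficient of the baseline value at 1 instead of estimating it. For any correlation below 1 the result is less precise than adjusting for baseline. When the correlation is below 0.5 it is also less precise than ignoring baseline altogether.

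A modest correlation is plausible for two of the three primary outcomes. Intake rests on two days and activity on five, the two rounds of measurement are separated by a 6–8 month intervention, and the Limitations section concedes that children's "physical activity level and dietary intake can vary from one day to the next". The article gives no comparable reason to expect a low correlation for the motor-skill test.

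Two things are at stake: power, in a trial planned at 80%, and sensitivity to chance baseline differences between arms with only 61 centres.

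**Working it through.** **Inputs from Target population and sampling.** 350 children analysed per arm; difference 10%; SD 40%; "α = 0.05, intra-class correlation of 0.02"; multiple correlation 0.15; 62 planned centres. The plan's claim is that this "will provide 80 % power to detect a 10 % between-group difference in outcome".

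**Assumptions not in the article.** A two-sided test; a normal approximation; a baseline to follow-up correlation r from 0.3 to 0.7, the same within and between centres; equal variance at the two time points.

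**Step 1: reproduce the plan's figure.**
- Children per centre: 700/62 = 11.29.
- Design effect: 1 + (11.29 − 1) × 0.02 = 1.206.
- Effective number per arm with 0.15 read as R²: 350/1.206 × (1 − 0.15) = 246.7.
- Effective number per arm with 0.15 read as R: 350/1.206 × (1 − 0.15²) = 283.7.
- Standardised difference: 10/40 = 0.25.
- Power = Φ(0.25 × √(n_eff/2) − 1.96) = 79.3% with R² = 0.15, and 84.6% with R = 0.15.

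The stated 80% is therefore reproduced on the first reading and slightly exceeded on the second. Both are carried forward as a range.

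**Step 2: variance under the two analyses.** In units of the single-time-point variance:
- unadjusted change: 2(1 − r)
- baseline-adjusted: 1 − r²
- ratio: 2(1 − r)/(1 − r²) = 2/(1 + r)

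**Step 3: power if 40% is a single-time-point SD.** Power = Φ(0.25 × √(n_eff/(2f)) − 1.96), with f the variance factor from step 2. For example, at r = 0.3 with n_eff = 246.7, change gives 0.25 × √(246.7/2.8) − 1.96 = 0.39, hence 65%. Adjusted gives 0.25 × √(246.7/1.82) − 1.96 = 0.95, hence 83%.

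| r | f, change | f, adjusted | Ratio | Power, change | Power, adjusted |
|---|---|---|---|---|---|
| 0.3 | 1.40 | 0.91 | 1.54 | 65–71% | 83–88% |
| 0.4 | 1.20 | 0.84 | 1.43 | 72–78% | 86–90% |
| 0.5 | 1.00 | 0.75 | 1.33 | 79–85% | 89–93% |
| 0.7 | 0.60 | 0.51 | 1.18 | 95–97% | 97–99% |

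**Step 4: power if 40% is instead the SD of change.** Unadjusted change then has the planned 79–85%. Baseline adjustment multiplies the variance by (1 + r)/2, and power becomes 93–96% at r = 0.3, 89–93% at r = 0.5 and 85–90% at r = 0.7.

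**Step 5: if baseline is in the model.** Regressing change, or the follow-up value, on arm and baseline gives the same treatment effect and standard error. The loss in step 2 arises only when the baseline covariate is left out.

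**The case against.** The strongest objection is that the article does not say what the concern needs it to say. Greater increases is the research question, echoing the study objectives, and need not mean a change-score outcome. The covariate list is open-ended and may include baseline. This is also a journal article, and the exact model can reasonably be left to an analysis plan. This stands in part: a reader might infer that baseline adjustment has been ruled out, and the text does not support that. What remains is that the article does describe the model, and its description leans towards unadjusted change. The section on complementary measures presents confounders as something beyond the main measures, so the open-ended term more naturally covers further background variables than the baseline outcome.

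The second objection is that the power loss depends on unknowns. This stands. The article gives no correlation and does not say what the 40% SD refers to. At r = 0.5 unadjusted change still delivers the planned power, and at r = 0.7 it comfortably exceeds it. A reader might infer that power is lost on every primary outcome; the documents do not show that.

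The third concerns bias, and it also stands. Under randomisation a change-score comparison is unbiased on average, and a chance imbalance matters only conditionally on the baselines that occurred. It is tempting to add that baseline adjustment would cure differences arising from recruitment after allocation. The sampling section has centres consenting before they are allocated, with only the parental invitations described afterwards. If selective enrolment of children did produce stable differences between arms, baseline adjustment would not reliably remove them.

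**Conclusion.** The point holds as one of precision and of handling chance baseline imbalance. As worded, the analysis section permits a change comparison without the baseline covariate. For child-level outcomes that would inflate the variance by 2/(1 + r), from 1.54 at r = 0.3 to 1.18 at r = 0.7.

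The consequence for power is conditional. It falls below plan only if the 40% SD is a single-time-point SD and r is below about 0.5. Otherwise the planned power holds and adjustment adds to it. The figures assume the same r within and between centres, so the gain in the multilevel model may differ. They do not apply to the opportunity outcomes, which are measured at centre level. Some children will lack one of the two measurements, since about 5% attrition and multiple imputation are foreseen. The documents do not support a claim that the planned analysis is biased or that baseline adjustment has been rejected.

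**What to change.** State in the Data analysis section, or in the analysis plan before the outcome data are analysed, that each child-outcome model regresses the follow-up value on arm, the baseline value of the same outcome, the stratification factors (province, urban or rural location, language) and a centre random intercept. Change may be kept as the dependent variable if that suits the reporting, provided the baseline value is a covariate. State also whether the 40% SD refers to a single time point or to change.

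The cost is wording only. The baseline measures are already scheduled in both arms, and the article reports that data collection is still under way. The change should be justified by precision and chance imbalance, and not presented as protection against selective recruitment of children after their centre's allocation.

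### Centre-provided opportunities have one value per centre per wave, yet the plan puts them in the same children-within-centre regression as the child outcomes; they need a centre-level analysis

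*Protocol article*

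**What the plan says.** The Data analysis section of the protocol article describes one regression approach for all main objectives. It compares participants in the two arms on whether they "had greater increases in ECC-provided opportunities for physical activity, ECC-provided opportunities for healthy eating, in physical activity levels", and continues with healthy eating and physical literacy. The clustering structure is then fixed for all of these at once: "A multilevel approach will be used in each model to account for clustering that could result from children attending the same ECC". The covariates named are a child characteristic and family characteristics: "Potentially confounding variables (i.e., age, parental education, household income, etc.) will be included in the models".

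The measurement sections show that the opportunity outcomes are recorded for the centre.

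- Early childcare centre environment: "The NAP SACC is filled out independently by two research assistants in each ECC over the course of 2 consecutive days". The two raters end with one agreed score: "Differences in item scores are discussed between research assistants, who then come to a consensus".
- Quality of food served to children: "Menus and recipes for mixed dishes are collected from each ECC".
- The Main outcome measures section places the measures before and after the intervention period, so there are two waves.

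Opportunities are the first specific objective under Study objectives. The only sample size calculation, under Target population and sampling, counts children: 700 "participants divided into two groups of 350 participants will provide" 80% power, with an intra-class correlation of 0.02, for an outcome that is not named.

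**The concern.** The model stated for every outcome has children as its lowest level. For a NAP SACC or menu score, every child in a centre carries the same number. Repeating it across children adds rows and no information, and it leaves the model without the child-level variation that it is built to separate from centre-level variation.

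Two things are at stake for objective 1. First, the fit may fail, or may return a standard error that is much too small while reporting success. Second, with no separate precision statement, a null result on opportunities could be read as though the 80% power applied to it.

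**Working it through.** **Inputs.** From Target population and sampling: 61 centres, 1:1 allocation of centres within stratum, 350 children per arm, difference 10, SD 40, alpha 0.05, intra-class correlation (ICC) 0.02, multiple correlation 0.15. Assumed: a two-sided test and a 31 v 30 split of centres; the article states neither.

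**Step 1. Reproduce the plan's own figure.** Unclustered size per arm: 2 × [(1.960 + 0.842) × 40/10]² = 251.2. With 700/62 = 11.3 children per centre, the design effect is 1 + 10.3 × 0.02 = 1.206. Reading the collinearity term as 1/(1 − 0.15) = 1.176 gives 251.2 × 1.206 × 1.176 = 356 per arm, within 2% of 350 (power with 350 is 79.3%). Using 20 children per centre and 1/(1 − 0.15²) gives 355. Either way, the 350 is a child-level calculation with a small ICC.

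**Step 2. Structure of the opportunity outcomes.** Write the score of child j in centre i as y_ij = y_i for all j. The within-centre variance is then 0 and the ICC is 1. The design effect becomes 1 + (m − 1) × 1 = m = 700/61 = 11.5, so 700 children carry 700/11.5 = 61 independent values per wave. A child covariate that varies inside a centre cannot predict a constant, so its within-centre slope is zero and the named confounders do no adjusting there.

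**Step 3. What a fit does.** Simulated data: 61 centres × 12 children, no arm effect, outcome constant within centre, random intercept plus one child covariate, fitted in Python's statsmodels.

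| Analysis | Arm standard error | One row per centre |
|---|---|---|
| Random intercept, exactly constant outcome (one data set) | 0.0633 | 0.2226 |
| Generalised least squares as ICC approaches 1 | 0.2226 | 0.2226 |
| Random intercept, within-centre noise SD 0.05 (another data set) | 0.2437 | 0.2441 |

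In the first row the ratio is 0.0633/0.2226 = 0.28, and the software reported convergence. Over 30 null data sets of that kind the mean ratio was also 0.28, and 17 of 30 tests rejected at 5%. The cause is a failed variance estimate: the fitted between-centre variance was about 1/12 of its true value. The other two rows show that a properly estimated model gives centre-level precision.

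**Step 4. Precision with the centre as the unit.** The standard error of the difference is SD × √(1/31 + 1/30) = 0.256 SD. The normal approximation for 80% power gives 2.802 × 0.256 = 0.72 SD; the noncentral t on 59 degrees of freedom gives 0.73 SD. Adjusting for baseline with correlation r multiplies this by √(1 − r²). The article gives no r, so as a range:

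| Assumed r | Detectable difference, 80% power |
|---|---|
| 0 | 0.73 SD |
| 0.5 | 0.63 SD |
| 0.7 | 0.52 SD |
| 0.9 | 0.32 SD |

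**The case against.** The strongest reply is that the paragraph is a condensed summary of five outcomes, that it nowhere says centre scores will be copied to children, and that the unit of analysis for a centre measure is a detail for the analysis plan. Part of this stands: the wording can be read as modelling the nesting only where there is nesting. But the article does not leave the matter open. It names the opportunity outcomes, compares participants, and applies the child-in-centre structure to each model. That is a stated mismatch with its own measurement sections.

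A reader might go further and infer any of three things that the documents do not support.

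- **That the test of objective 1 will have a grossly inflated type I error.** If each score were repeated for 12 children and clustering ignored, standard errors would be too small by √12 = 3.46 and the error rate would be 2 × [1 − Φ(1.96/3.46)] = 57%. But the plan commits to accounting for clustering, and step 3 shows that a sound fit does so. The inflation depends on the software.
- **That the protocol promises 80% power for opportunities and delivers 16%.** Power at 0.25 SD (10/40) with 31 v 30 centres is indeed 16%. The sample size section, however, makes no claim about centre-level outcomes, and 0.25 SD was not set for centre scores. An intervention aimed at centre practice might move them more.
- **That all of objective 1 rests on 61 values.** Educator questionnaires can give several values per centre. Their clustering is educators within centres, which the child-based wording does not describe either.

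It also stands that the Abstract's primary outcomes (accelerometry, TGMD-II and plate waste) are all child-level, so no primary comparison is affected.

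**Conclusion.** The point holds for opportunities measured by the NAP SACC and by menus. The stated children-within-centre model is degenerate for outcomes with one value per centre per wave, and the stated 80% power does not describe them. Both conclusions follow from the article's own text and need no assumption about software. Standard errors that are too small are a real risk, and can arise without a warning, but they are not a necessary result of the plan.

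The size to carry forward is a detectable difference of about 0.73 SD with 80% power, assuming a two-sided 5% test, 31 v 30 centres and no baseline adjustment. It falls to between 0.63 and 0.32 SD for assumed baseline correlations of 0.5 to 0.9. The matter is confined to objective 1.

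**What to change.** Amend the Data analysis section as follows.

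- **NAP SACC nutrition and physical activity scores, and menu quality:** one row per centre. Regress the follow-up score on arm, baseline score and the stratification factors (province, urban or rural location, language), and use the t distribution on centre-level degrees of freedom. With the three factors as main effects this leaves 61 − 6 = 55.
- **Educator questionnaires:** analyse at educator level with a random effect for centre.
- **Child outcomes:** keep the child multilevel model as it stands.
- **Power:** state that the 80% applies to child-level outcomes only, and give the centre-level detectable difference (about 0.73 SD before baseline adjustment, with the assumptions above).

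The cost is wording. No new data are needed, and the Trial status section describes data collection as ongoing, so the change could precede analysis. The downside is a less favourable precision statement for objective 1.
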